### Assignment and blinding

Block randomization is conducted in a 1:1 ratio to receive either Yirui capsules or the placebo. As this study is a multicenter study, blocked randomization is conducted for each center. The randomization sequence table generated by Statistical Analysis System (SAS) Version 9.2 was provided by a specific statistical researcher who does not participate in the clinical trial. The statistical researcher randomly distributes the number to the research products. The random numbers are kept in opaque sealed envelopes and sent to research centers. Afterwards, clinical investigators randomly assign the random number based on enrollment order and provide the corresponding drug. Choosing the number intentionally is strictly forbidden. The random number is fixed during the whole study. The blinding base containing the randomization sequence, parameters of sequence, and random number is sealed in duplicate and reserved by the principal investigator and product registration applicant. Patients and clinical investigators can only be aware of the individual random number. Treatment assignments are not exposed and are blinded to patients and any clinical investigators involved in this trial until the entire study is completed. At the last visit, all participants and clinical investigators will finish a questionnaire about which treatment (Yirui capsule group or placebo group) the patients received to assess the success of blinding. Emergency letters containing random number and treatment assignment would also be prepared by a specific statistical researcher. Code breaks are only allowed in emergency situations when practical intervention is compulsory for further management of the participant.

### Sample size calculation

The sample size calculation was based on the primary outcome measure. Previous studies of Chinese herbal medicine (CHM) on hyperlipidemia had detected a difference of at least 20 % between Yirui capsule and placebo. Assume that placebo effect is about 10 %. The sample size in each group was determined by using the formula derived by Whitley et al. [32]:$$ n=\frac{\left[{\mathrm{p}}_1\left(1-{\mathrm{p}}_1\right)+{\mathrm{p}}_2\left(1-{\mathrm{p}}_2\right)\right]}{{\left({\mathrm{p}}_1-{\mathrm{p}}_2\right)}^2}\times {C}_{\mathrm{p},\kern0.5em \mathrm{power}} $$

For type I: α = 0.05, β = 0.10; power (1-β) = 90 %; p_1_ = 10 %, p_2_ = 30 %; and C _p, power_ = 10.5; the two-tailed level α and power were set at 0.05 and 80 %, respectively. Seventy-five subjects were needed in each group. Estimating about 20 % dropouts, the number of each group was 90, and a total of 180 subjects were needed for this study.

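### The printed sample-size formula gives 79 per group, not 75, and the same sentence sets power at both 90 % and 80 %, so the 75 matches neither target

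*Protocol article*

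**What the plan says.** The Protocol article, Sample size calculation, bases the trial's size on the primary outcome, the proportion of participants whose LDL-C falls by 30 % at week 24. It assumes a 10 % response on placebo and says that earlier studies "had detected a difference of at least 20 % between Yirui capsule and placebo". It prints the unpooled two-proportion formula, with p1 = 10 %, p2 = 30 % and C = 10.5.

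The error rates come next, in one sentence. The first half gives "α = 0.05, β = 0.10; power (1-β) = 90" per cent. The second half says "the two-tailed level α and power were set at 0.05 and 80 %, respectively".

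The result is stated as "Seventy-five subjects were needed in each group". The allowance for loss follows: "Estimating about 20 % dropouts, the number of each group was 90, and a total of 180 subjects were needed for this study".

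Two other sections bear on the point. Assignment and blinding fixes equal allocation ("Block randomization is conducted in a 1:1 ratio to receive either Yirui capsules or the placebo"). Statistical analysis plans a two-sided 0.05 test by intention to treat (ITT), with missing values filled by last observation carried forward (LOCF).

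**The concern.** Every input to the calculation is printed, so a reader can check it, and it does not check. The per-group figure does not come out of the formula. Two different powers are given for one design. The allowance for loss does not return the number it is meant to protect.

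This paragraph is the only justification given for recruiting 180 patients, and the only statement of how likely the trial is to detect the assumed difference. Someone interpreting a non-significant result will turn to it and find two powers and a sample size that belongs to neither.

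**Working it through.** **Inputs**, all from the Protocol article, Sample size calculation: p1 = 0.10, p2 = 0.30, two-sided α = 0.05, C = 10.5, power 90 % and 80 %, loss about 20 %, final size 90 per group.

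**1. The plan's own formula.**
n = [p1(1 − p1) + p2(1 − p2)] / (p1 − p2)² × C
- Numerator: 0.10 × 0.90 + 0.30 × 0.70 = 0.09 + 0.21 = 0.30
- Denominator: 0.20² = 0.04
- n = 7.5 × 10.5 = 78.75, so **79 per group**

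The stated 75 is not reproduced. It would need C = 75/7.5 = 10.0. Rounding does not explain this, because the unrounded constant for two-sided 0.05 and 90 % power is 10.507 and gives 78.8.

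**2. The second power statement.** For 80 % power the constant is 7.85 (7.9 if rounded).
- 7.5 × 7.849 = 58.9, so 59
- 7.5 × 7.9 = 59.25, so 60

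So 75 is not the 80 % figure either. The printed β = 0.10 and C = 10.5 both belong to 90 %.

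**3. Other two-sided methods**, in case a different one was used:

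| Method | 90 % power | 80 % power |
|---|---|---|
| Printed formula | 79 | 59 |
| Arcsine | 79 | 60 (59.01 rounded up) |
| Pooled under the null | 82 | 62 |
| Pooled, continuity-corrected | 92 | 72 |

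None gives 75. A one-sided, continuity-corrected calculation at 90 % gives 77, but it contradicts both the printed formula and the two-tailed α.

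**4. Allowance for loss.**
- 75 × 1.2 = 90, which is the plan's figure
- 90 × 0.80 = 72, which is 3 below 75
- 1 − 75/90 = 16.7 %, the loss that 90 actually covers for a target of 75
- 75/0.80 = 93.75, so 94; 79/0.80 = 98.75, so 99

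**5. Power that the design delivers.** Power = Φ(|p1 − p2| / √{[p1(1 − p1) + p2(1 − p2)]/n} − 1.96). The exact column is the uncorrected chi-squared test with binomial probabilities summed.

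| Analysed per group | Rates | Normal approximation | Exact |
|---|---|---|---|
| 72 | 10 % vs 30 % | 87.3 % | 87.4 % |
| 75 | 10 % vs 30 % | 88.5 % | 88.5 % |
| 79 | 10 % vs 30 % | 90.1 % | 90.2 % |
| 90 | 10 % vs 30 % | 93.4 % | 93.2 % |
| 90, with 20 % dropouts as non-responders | 8 % vs 24 % | 85.1 % | 85.2 % |

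For the last row, 0.80 × 10 % = 8 % and 0.80 × 30 % = 24 %. The power is then Φ(0.16/√(0.256/90) − 1.96) = Φ(3.00 − 1.96) = 85.1 %.

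**The case against.** The arithmetic is hard to dispute; its consequence is not. Four points can be made.

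First, Statistical analysis specifies ITT with LOCF, so dropouts stay in the primary analysis and the number analysed is nominally 90 per group, not 72. At the assumed rates that gives about 93 %. This stands. The 72 shows that the allowance misses the paragraph's own target of 75, but it is not the planned analysis set. The 93 %, however, requires dropouts to respond as often as completers. Lipids are measured at every visit, so a carried-forward value may or may not be a response. Power then plausibly lies between about 85 % and 93 %, a range that contains 90 %.

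Second, if 80 % was the target, 180 patients are more than enough. This also stands. Even with a continuity-corrected chi-squared test, the 72-per-group case gives 81.6 % and the non-responder case 80.3 %. Since 60/0.80 = 75, the 75 might be an 80 % figure already inflated for loss. The protocol does not say so; on that reading it inflates twice and prints the wrong β and C.

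Third, the loss is only about 20 %, and multiplying by 1.2 is a common shortcut. That is fair. The shortfall is 3 per group, which makes this the minor part of the point.

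Fourth, a reader might infer that the trial is underpowered, or that it must recruit 99 per group. The documents do not support either. No scenario above falls below 80 %, and 99 is needed only if 90 % is confirmed as the target and dropouts are left out of the analysis, which is not what is planned.

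**Conclusion.** The paragraph is wrong as written. Its formula and inputs give 79 per group, 4 more than stated. Its two powers contradict each other, and 75 corresponds to neither (79 for 90 %, 59 to 60 for 80 %). As a lesser matter, 90 per group does not preserve 75 after a 20 % loss.

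The effect on the trial is limited. For 10 % versus 30 % at two-sided 0.05, 90 randomised per group gives about 93 %, 87 % or 85 % power, depending on how dropouts enter the analysis. The 80 % statement is exceeded in each case. The 90 % statement is not assured under the plan's own 20 % loss, but it cannot be called missed either, because LOCF may leave the true figure on either side of it. These results rest on the protocol's response rates and on equal loss in both groups. The case for correction is that the justification for 180 cannot be reproduced and the design power is undefined, not that the trial is too small.

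**What to change.** Keep 180 patients and rewrite the paragraph as follows.

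- Declare one target power, with the β and C that belong to it, and delete the other. The choice is the trial team's; the printed β = 0.10 and C = 10.5 match 90 %.
- Replace 75 with the formula's value: 79 for 90 %, or 59 to 60 for 80 %.
- Do not present 90 as a 20 % loss allowance on 75 or 79, since division by 0.80 gives 94 or 99. Give 90 as the number to be randomised.
- Report the power of 90 per group for 10 % versus 30 % at two-sided 0.05: about 93 % if all 90 are analysed under ITT with LOCF at the assumed rates, about 85 % if 20 % dropouts count as non-responders (8 % versus 24 %), and about 87 % if only 72 per group are evaluable.

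The cost is wording only: no extra patients, and no change to endpoint, test or recruitment. The one drawback is that the stated power may become slightly less favourable than 90 %. Trial status reports that recruitment was under way and that no participant had completed treatment at submission, so on that timing the correction could be made before primary outcome data existed.

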### Statistical analysis

All effectiveness and safety evaluations will be conducted according to the intention-to-treat (ITT) principle. The last-observation-carried-forward method will be applied to deal with missing values. SAS (Version 9.2) will be utilized to analyze the data, and the statistical significance is defined as a two-sided *P* value of <0.05. For measurement data, the mean, standard deviation (SD), maximum, minimum, P25, median, and P75 will be reported. For paired measurement data, the mean difference, SD, and confidence interval (CI) will also be reported. As to enumeration data and ranked data, frequency distribution and corresponding percentage are compulsory. Baseline data of the two arms (e.g., demographic data) will undergo descriptive and inferential analyses. Intra-group efficacy comparisons before and after the treatment will be conducted by using the paired *t* test or Wilcoxon signed rank test for quantitative variables and the chi-squared test for qualitative variables. Efficacy difference between groups will be assessed with the utilization of the two-sample *t* test or corresponding non-parameter methods for quantitative variables, the chi-squared test for qualitative variables, and the Wilcoxon rank sum test for rank variables. For the primary outcome, the mean difference with two-sided 95 % CI will be reported. Statistic effectiveness is defined as the lower limit of 95 % CI above 0. Clinical effectiveness needs to be assessed after combining with clinical significance. For the consideration of the multicenter character, a covariance model is used to evaluate the center effect for the primary variable. Other secondary outcomes will take no account of the center effect. In addition, the chi-squared test will be utilized to analyze the rate of adverse events between the two arms. A table will be generated to enumerate and describe the characters of all adverse events during the study.

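### The dropout allowance assumes dropouts leave the analysis, but the plan keeps them by ITT with LOCF; the claimed 90 % power is not assured either way

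*Protocol article*

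**What the plan says.** Three statements in the protocol article bear on this.

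- **Sample size calculation, inputs.** The calculation uses "α = 0.05, β = 0.10; power (1-β) = 90 %; p_1_ = 10 %, p_2_ = 30" (the last figure is a percentage), with a constant of 10.5. The same sentence goes on to say that "the two-tailed level α and power were set at 0.05 and 80 %, respectively". The 20-point difference is credited to previous studies that "had detected a difference of at least 20 % between Yirui capsule and placebo". The section does not say whether the 10 % and 30 % describe completers or everyone randomised.
- **Sample size calculation, dropout step.** The result of 75 per group is raised: "Estimating about 20 % dropouts, the number of each group was 90, and a total of 180 subjects were needed for this study".
- **Analysis rule, in the section on statistical analysis.** One rule covers efficacy and safety alike: "All effectiveness and safety evaluations will be conducted according to the intention-to-treat (ITT) principle". The next sentence names LOCF as the method for missing values.

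Three other sections matter. The primary outcome is the proportion with a 30 % fall in LDL-C from baseline at week 24 (Outcomes). The lipid profile is taken at every visit (Outcomes). The visits are at weeks 0, 4, 12, 24 and 28 (Study design).

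**The concern.** The dropout step and the analysis rule describe different comparisons. Enlarging a group to offset dropout replaces people who supply no data to the test. Under ITT with LOCF nobody is removed: a participant who leaves early stays in the denominator and is classed as responder or non-responder on the last LDL-C value available. What may need adjusting is then the difference between the arms, and the sample size section does not adjust it. If dropouts on Yirui respond less often than completers, the Yirui rate in the planned analysis falls below 30 %, and the extra 15 per group offset this only in part.

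At stake is how the result is read. A non-significant primary result would be judged against a claimed 90 % power that the planned comparison may not have. The mismatch would remain if the other arithmetic in the section were corrected.

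**Working it through.** **Inputs.** From Sample size calculation: two-sided α 0.05, placebo rate 10 %, Yirui rate 30 %, C = 10.5, 20 % dropout, 75 raised to 90 per group. From Assignment and blinding: 1:1 allocation. From Statistical analysis: ITT, LOCF and a chi-squared test for qualitative variables. Assumed here because the document does not give them: equal dropout in the two arms, and how dropouts respond.

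**Step 1: the plan's own figure.** The printed formula gives

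[0.10 × 0.90 + 0.30 × 0.70] / 0.20² × 10.5 = 7.5 × 10.5 = 78.75, so 79 per group.

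The plan states 75. At 80 % power (C about 7.85) the formula gives 7.5 × 7.85 = 58.9, so 59. The 75 is therefore not reproduced at either power, but it lies close to the 90 % result and far from the 80 % one.

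**Step 2: the dropout step.** 75 × 1.2 = 90 reproduces the plan. Losing 20 % of 90 leaves 90 × 0.8 = 72, not 75. Keeping 75 would need 75 / 0.8 = 93.75, so 94.

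**Step 3: power if dropouts leave the analysis.** The normal approximation is

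power = Φ( (pY − pP) / √{[pP(1 − pP) + pY(1 − pY)] / n} − 1.96 ).

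With n = 72: 0.20 / √(0.30 / 72) = 3.098; 3.098 − 1.96 = 1.138; power 87.3 %. Exact enumeration of the uncorrected chi-squared test (binomial probabilities of all outcome pairs significant in favour of Yirui) gives 87.4 %. With 75 per arm the figure is 88.5 % by both methods.

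**Step 4: power if dropouts stay, 90 per arm.** If 10 % and 30 % are completer rates, each arm's ITT rate is 0.8 × completer rate + 0.2 × dropout rate.

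| Assumed response of dropouts | Placebo | Yirui | Exact power | Normal approximation |
|---|---|---|---|---|
| Placebo rate in both arms | 10 % | 0.8 × 30 + 0.2 × 10 = 26 % | 81.2 % | 81.5 % |
| None respond | 0.8 × 10 = 8 % | 0.8 × 30 = 24 % | 85.2 % | 85.1 % |
| Half the effect kept | 10 % | 0.8 × 30 + 0.2 × 20 = 28 % | 88.3 % | 88.5 % |
| Same as completers, or the rates are already ITT rates | 10 % | 30 % | 93.2 % | 93.4 % |

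Example, first row: 0.16 / √{(0.09 + 0.1924) / 90} = 2.856; 2.856 − 1.96 = 0.896; power 81.5 %. A pooled-variance approximation gives figures about one point lower (80.3 % in the first row).

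**Step 5: where 90 % is reached.** Let dropouts on Yirui keep a share k of the 20-point effect and dropouts on placebo respond at 10 %. The Yirui rate is then 26 % + 4k points. At k = 2/3 it is 28.7 %, and exact power is 90.1 %. So 90 % requires dropouts to keep roughly two thirds of the effect.

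**Step 6: what LOCF settles.** A participant lost before week 4 has only the baseline value, hence zero change, and is a non-responder by construction. One lost after week 4 or week 12 is scored on an on-treatment value from that visit. The document does not say how dropout is spread over time or how much of the week-24 response is present at weeks 4 and 12, so it does not fix k.

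The range in Step 4 is illustrative and not a bound. If dropouts on Yirui never responded while those on placebo responded at 10 % (10 % versus 24 %), power would be about 72 %. That asymmetric case is harsher than anything the document suggests.

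**The case against.** A reader might infer that the 90 % power is true of completers and that the ITT analysis forfeits it. The documents do not support that, for four reasons.

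- **Completers do not have 90 % either.** At 10 % versus 30 %, 75 per arm gives 88.5 % and the 72 left from 90 give about 87 %. Measuring a loss from 90 % overstates what ITT costs. Against 88.5 %, the two adverse cases lose about 3 and 7 points (88.5 − 85.2 and 88.5 − 81.2), and the half-effect case loses almost nothing.
- **The rates are not labelled.** The 20-point difference comes from previous studies whose analysis sets are not described. If 10 % and 30 % are ITT rates there is no dilution, and 90 per arm gives about 93 %.
- **LOCF is not a rule that counts every dropout as a failure.** Later dropouts are scored on week 4 or week 12 values and may still count as responders.
- **The 80 % printed in the same section is met in all four cases tabulated.**

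It can also be said that adding patients for dropout alongside an ITT analysis is common and conservative practice.

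All four points stand, and they limit the claim. They do not remove it. If the rates are ITT rates, the dropout addition has no function under the stated analysis; if they are completer rates, the effect should have been adjusted. The sample size and analysis sections do not fit together on either reading. The 80 % does not rescue the calculation: β = 0.10 and C = 10.5 both belong to 90 %, and the formula at 80 % would give 59.

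**Conclusion.** The mismatch is in the text and holds. The dropout allowance treats dropouts as absent from a test in which the plan keeps them. The claimed 90 % is not assured: power is about 87 % if dropouts leave, and about 81 to 93 % if they stay under ITT/LOCF with 90 per arm, reaching 90 % only if dropouts keep roughly two thirds of the effect. These figures assume 20 % dropout in each arm and the responder rates stated in the plan.

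It would go too far to conclude that the trial is underpowered. Whether there is a shortfall in the planned analysis, and how large, depends on which population the rates describe and on how dropouts respond under LOCF, and the document gives neither. This is a modest defect in how the sample size is justified. It does not call for more patients or a different analysis.

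**What to change.** Keep 180 participants and the ITT/LOCF analysis. In the sample size section:

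1. State one power target in place of the two printed.
2. Say whether 10 % and 30 % are rates among completers or among all randomised participants.
3. Replace the 90 % with the power of the comparison actually planned, for example: with 90 per group analysed by ITT with LOCF and 20 % dropout in each group, power is about 81 % if dropouts respond at the placebo rate in both groups, 85 % if none respond, and 93 % if they respond like completers.

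The 75-versus-79 result and the multiplication by 1.2 can be corrected in the same edit. The cost is a few words in one section and a slightly less favourable stated power. As recruitment is under way, the restatement can be carried into the analysis plan and the results report without affecting trial conduct.

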### Statistical analysis

All effectiveness and safety evaluations will be conducted according to the intention-to-treat (ITT) principle. The last-observation-carried-forward method will be applied to deal with missing values. SAS (Version 9.2) will be utilized to analyze the data, and the statistical significance is defined as a two-sided *P* value of <0.05. For measurement data, the mean, standard deviation (SD), maximum, minimum, P25, median, and P75 will be reported. For paired measurement data, the mean difference, SD, and confidence interval (CI) will also be reported. As to enumeration data and ranked data, frequency distribution and corresponding percentage are compulsory. Baseline data of the two arms (e.g., demographic data) will undergo descriptive and inferential analyses. Intra-group efficacy comparisons before and after the treatment will be conducted by using the paired *t* test or Wilcoxon signed rank test for quantitative variables and the chi-squared test for qualitative variables. Efficacy difference between groups will be assessed with the utilization of the two-sample *t* test or corresponding non-parameter methods for quantitative variables, the chi-squared test for qualitative variables, and the Wilcoxon rank sum test for rank variables. For the primary outcome, the mean difference with two-sided 95 % CI will be reported. Statistic effectiveness is defined as the lower limit of 95 % CI above 0. Clinical effectiveness needs to be assessed after combining with clinical significance. For the consideration of the multicenter character, a covariance model is used to evaluate the center effect for the primary variable. Other secondary outcomes will take no account of the center effect. In addition, the chi-squared test will be utilized to analyze the rate of adverse events between the two arms. A table will be generated to enumerate and describe the characters of all adverse events during the study.

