**Table 1 Tab1:**
[figure not shown]
Schedule of enrollment, intervention, and assessments

There will be five visits for each participant in week 0, week 4, week 12, week 24, and week 28. At the first visit, patients will have their general data recorded and will be given the prescription. Then, patients will take the prescription to the specified pharmacy and receive either Yirui capsules or the placebo. 4 weeks and 12 weeks after the first visit, patients will come back for clinical evaluation and medication. Visit 4 is planned for the end of the treatment period (week 24); at this visit patients will only receive clinical evaluation. Afterwards, the patients will stop taking Yirui capsules or the placebo for another 4 weeks and then come back for clinical evaluation.

The study protocol was approved by the ethics committees of the First Affiliated Hospital of Jinan University, Guangdong No. 2 Provincial People’s Hospital, Hexian Memorial Affiliated Hospital of Southern Medical University, and the Fifth Affiliated Hospital, Sun Yat-sen University (Approval Version: LWXJ.YRJN-HBT-V1.0), and informed consent was obtained from each participant.

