#### Exclusion criteria

Patients were excluded for one or more of the following reasons: (1) TG ≥5.65 mmol/L; (2) combined with hypertension, diabetes, or thyroid dysfunction; (3) combined severe primary diseases (i.e., cardiovascular and cerebrovascular diseases, liver and kidney diseases, hematopoietic system dysfunction), or malignant tumor, or mental disorder, or other serious complicated disease; (4) documented hyperlipidemia-induced target organ damage (i.e., atherosclerosis and CHD) with need to maintain treatment to dyslipidemia; (5) secondary hyperlipidemia, drug-induced hyperlipidemia, homozygous hypercholesterolemia; (6) pregnancy; (7) alanine aminotransferase (ALT) and/or aspartate aminotransferase (AST) ≥3 times the upper limit of normal (ULN); (8) creatinine (CREA) ≥1.5 times the ULN; (9) combined with active peptic ulcer or gastrointestinal hemorrhage; (10) allergy to components of product or allergic constitution; (11) hospitalized; (12) cannot obey therapeutic lifestyle modification.

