### Outcomes

Clinical investigators will obtain written informed consent and collect basic data such as gender, age, height, weight, and medical history at baseline. For safety concerns, besides the basic data, vital signs will be taken and laboratory examinations conducted, for instance, blood pressure, heart rate, routine blood tests (e.g., red blood cell (RBC), white blood cell (WBC), hemoglobin (Hb), etc.), liver and kidney function tests (e.g., ALT, AST, CREA, etc.), pregnancy test, and 12-lead electrocardiogram (ECG). Except for the pregnancy test, which only needs to be conducted in the first visit (week 0, baseline), other tests should be conducted routinely at every visit during the treatment period (the ECG is not mandatory at the second visit (week 4)). Also, any adverse events such as abdominal discomfort should be monitored and recorded during the whole study.

Participants need to receive a blood lipid profile test which contains the following indexes: TC, TG, HDL-C, LDL-C, apolipoprotein A (apoA), apolipoprotein B (apoB), and non-high-density lipoprotein cholesterol (non-HDL-C). The blood sample should be collected after at least a 12-hour fast, and the last meal before the blood sampling should not contain greasy food. In order to evaluate the health status of participants, the MOS 36-Item Short-Form Health Survey (SF-36) is utilized [26–28]. In addition, for assessment of clinical symptoms, another symptomatic grading and quantifying scale is applied. Weight monitoring and diet evaluation are also two aspects that need to be conducted. All participants are required to complete the tests and scales mentioned above at every visit under the guidance and assistance of the clinical investigators. The results are recorded and compared within a group and between groups before and after intervention.

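### Safety is placed under ITT with unrestricted last observation carried forward, so undosed participants and pre-dose laboratory values can dilute or distort the safety comparison

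*Protocol article*

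**What the plan says.** The Statistical analysis section opens with one rule for both aims: "All effectiveness and safety evaluations will be conducted according to the intention-to-treat (ITT) principle". The next sentence reads "The last-observation-carried-forward method will be applied to deal with missing values". Neither sentence separates safety from effectiveness, and the article names no dosed or as-treated safety set. The safety analyses it names are that "the chi-squared test will be utilized to analyze the rate of adverse events between the two arms" and that "A table will be generated to enumerate and describe the characters of all adverse events during the study".

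Four other places bear on how these rules would work:

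- **Study design, visit description.** After the first visit "patients will take the prescription to the specified pharmacy and receive either Yirui capsules or the placebo", so supply is a separate step that a randomised participant could fail to complete.
- **Outcomes.** Apart from the pregnancy test, "other tests should be conducted routinely at every visit during the treatment period", with the ECG optional at week 4. With the stated visit schedule, this means blood tests at weeks 0, 4, 12 and 24. Adverse events "should be monitored and recorded during the whole study".
- **Exclusion criteria (7) and (8).** Criterion (7) removes anyone with "alanine aminotransferase (ALT) and/or aspartate aminotransferase (AST) ≥3 times the upper limit of normal (ULN"; criterion (8) removes anyone with creatinine at or above 1.5 times the ULN.
- **Data collection and handling of withdrawal and dropout.** Severe adverse effects and hypersensitivity are listed reasons for leaving the study.

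**The concern.** ITT and carrying values forward are rules for effectiveness. Applied to safety, they raise two separate problems.

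The **denominator**: someone who never took a capsule cannot have an event caused by it, yet under ITT counts as one more participant in the arm without a treatment-caused event.

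The **laboratory values**: a participant who leaves before week 4 has only a pre-dose ALT, AST and creatinine. Unrestricted LOCF presents those as week 4, 12 and 24 results. By eligibility they cannot reach 3 times the ULN (ALT, AST) or 1.5 times the ULN (creatinine), so at those cut-offs the participant is shown as tested and clear when no on-treatment test was done.

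Safety is in the trial's title and its conclusion. The article makes this choice explicitly, so an analysis plan that followed it would inherit it.

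**Working it through.** The plan gives no figure for this point: no never-dosed share, no adverse event rates and no laboratory abnormality rates. The inputs it does give are 90 participants per group, 1:1 allocation, a two-sided 0.05 level, about 20 % dropout (0.20 × 90 = 18 per group) and the test schedule above. Everything else below is an assumption.

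**1. Denominator.** Let r be the event rate among dosed participants and f the never-dosed share, with no events counted in the undosed.

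- Rate shown under ITT = r × (1 − f).
- Risk difference shown = (r_active − r_placebo) × (1 − f), if f is equal in both arms.
- Risk ratio shown = r_active / r_placebo, unchanged if f is equal in both arms.

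With assumed rates of 20 % and 10 % among the dosed, and power for a two-sided 0.05 comparison of two proportions using 90 per arm (ITT) or 90 × (1 − f) per arm (dosed only):

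| f | ITT rates | Risk difference | Risk ratio | Power, ITT | Power, dosed only |
|---|---|---|---|---|---|
| 0 % | 20.0 % vs 10.0 % | 10.0 points | 2.0 | 0.467 | 0.467 |
| 2 % | 19.6 % vs 9.8 % | 9.8 points | 2.0 | 0.458 | 0.460 |
| 5 % | 19.0 % vs 9.5 % | 9.5 points | 2.0 | 0.445 | 0.448 |
| 10 % | 18.0 % vs 9.0 % | 9.0 points | 2.0 | 0.423 | 0.429 |
| 20 % | 16.0 % vs 8.0 % | 8.0 points | 2.0 | 0.378 | 0.389 |

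The last row is an extreme in which every expected dropout is undosed. The relative understatement of each rate equals f, and the power of the test hardly differs between the two sets.

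**2. Which laboratory values are carried.** The first on-treatment test is at week 4.

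- Leaves before week 4: the pre-dose value is carried. Assuming it is the value used for eligibility, it lies below the exclusion cut-offs. It may still lie above the ULN, because ALT or AST between 1 and 3 times the ULN is eligible.
- Leaves after week 4 or week 12: an on-treatment value is carried, normal or abnormal.

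**3. Direction of the LOCF effect.** Let q be the share abnormal at week 24 among completers, and h the share of dropouts whose last value is abnormal. With 20 % dropout, the week 24 rate under LOCF = 0.8q + 0.2h. For an assumed q of 5 %:

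- h = 0 %: 0.8 × 5 % + 0.2 × 0 % = 4 %
- h = 5 %: 4 % + 1 % = 5 %
- h = 10 %: 4 % + 2 % = 6 %
- h = 30 %: 4 % + 6 % = 10 %

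The observed-case rate is 5 % throughout. LOCF understates the week 24 rate only if dropouts' last values are abnormal less often than their week 24 values would have been.

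**The case against.** The strongest reply is that little of the planned safety analysis depends on these rules. The only comparison named is the adverse event rate, and LOCF has no natural role in whether an event occurred. The Outcomes section counts unusual laboratory findings as adverse events, so an abnormal result at week 4 or 12 is recorded and listed whatever is carried forward. This stands: it confines the LOCF problem to summaries of laboratory and vital-sign values. It does not touch the denominator of the adverse event test.

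The never-dosed share is also likely to be small, since product is supplied at enrolment, and an equal share in both arms leaves the risk ratio alone. This stands too, and limits the size.

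A third reply is that observed values alone could be worse at week 24, because the last abnormal value of someone who left for toxicity would drop out. That is fair against an observed-only table by itself. Counting anyone with an abnormal value at any post-baseline visit answers it.

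A reader might infer more than the article supports:

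- **That toxicity is certain to be understated.** Step 3 shows that the carried-forward rate can also exceed the observed one.
- **That the 20 % dropout measures the laboratory effect.** That figure covers the whole study; the article does not say how many leave before week 4, and only those participants carry a baseline value.
- **That a carried baseline value can never look abnormal.** This is so only at the exclusion cut-offs, which the article does not define as toxicity cut-offs.

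**Conclusion.** The point holds in a limited form. The article states, rather than leaves open, that safety follows ITT and that missing values are carried forward without restriction. Two consequences follow from the text: undosed participants enter the adverse event denominator, and those who leave before week 4 have pre-dose laboratory values presented as on-treatment results.

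The denominator effect is a relative understatement of each arm's rate equal to its own never-dosed share, and of the risk difference by the same share if it is equal between arms. That is 2 % to 10 % for an assumed f of 2 % to 10 %. The LOCF effect has no size or fixed direction that can be derived from the article. The supportable conclusion is that the rule may dilute or distort the safety comparison. The expected effect is modest, but the article gives no safety reason for the choice and correcting it is nearly free.

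**What to change.** Replace the opening rule of the Statistical analysis section with text to this effect:

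> Effectiveness is analysed by ITT, and any imputation applies to effectiveness only. Safety is analysed in all participants who took at least one capsule, by treatment actually received, using observed laboratory and vital-sign values with none carried forward. For each arm, the number with any post-baseline abnormal value and the number tested at each visit are reported.

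The table of all adverse events can stay as planned, so nothing recorded in an undosed participant is lost from view.

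No new data are needed: dose counting and laboratory tests at each treatment visit are already planned. The cost is slightly smaller safety denominators. The Trial status section says that nobody had completed treatment when the manuscript was submitted, so at that stage the change could have been made before unblinding.
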